### Participant timeline {13}

The project timeline showing schedule of enrolment, intervention and assessment is shown in Table 2. The project is for a 2-year period which has been divided into eight quarters and activities for each quarter indicated and the corresponding year.

**Table 2 Tab2:** The project timeline

S/N	Description of activity	Duration	Year	Quarter							
				1st	2nd	3rd	4th	5th	6th	7th	8th
1	Formation of team and coordination Planning and need assessment	3 months	1	X							
2	Finalizing protocol and manuals	2 months	1		X						
3	Hiring staff; selection and training of CORPs; identification of health Facilities and training of health workers	1 month	1		X						
4	Baseline studies and data analysis and interim report	2 months	1		X						
5	Preparation for intervention, Development of IEC	1 month	1		X						
6	Recruitment of patients	3 months	1			X					
7	Conducting follow-up visits	6 months	1 & 2				X	X			
8	Laboratory samples collected		1 & 2			X			X		
9	Mid-study report	1 month	1				X				
10	Post-intervention survey	3 months	2							X	
11	Final data analysis	2 months	2							X	
12	Final report writing	1 months	2								X

### Sample size {14}

The sample size will be determined using the superiority trial formula [33], power of 90% (*Z*_β_ = 1.28) and standard normal deviate (*Z*_α/2 =_ 1.96) corresponding to a 95% level of confidence.

Current literature indicates that only 30.0% [18] of those living with hypertension are controlled (p_1_). It is anticipated that the implementation of the intervention package will raise the percentage to 60.0% (p_2_). Based on these parameters, and adjusting for 10.0% attrition, a sample size of 50 persons living with hypertension will be required for each arm. This translates to 100 per LGA and 200 per state. Overall, 600 participants will be recruited for the intervention phase.

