### Implementation {16c}

This is a cluster-randomized trial. Clusters or communities will be randomized and not individual participants. Allocation will be done by the statistician while participants will be enrolled by CORPS and health workers at the primary health centres.

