### Methods in analysis to handle protocol non-adherence and any statistical methods to handle missing data {20c}

The use of CORPS who are based in the study communities and monthly home visit will help to minimize the occurrence of missing data and losses to follow-up. During analysis, sensitivity analyses will be carried out to assess the patterns of missing data and loss-to-follow-up so that appropriate decisions can be taken on whether multiple imputation methods need to be employed. The level of significance will be set at 5%.

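### The 50 per arm does not follow from the plan's own inputs and makes no allowance for clustering, so the stated 90% power is not delivered for the comparison it is attached to

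*Protocol article*

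**What the plan says.** Sample size {14} uses a superiority formula with a two-sided 5% level (Z = 1.96) and 90% power (Z = 1.28). It takes as the control rate that "only 30.0% [18] of those living with hypertension are controlled" and expects 60% under the intervention. It then states: "adjusting for 10.0% attrition, a sample size of 50 persons living with hypertension will be required for each arm". The next sentence scales this up: "This translates to 100 per LGA and 200 per state", and so to 600 in all. No intracluster correlation, cluster size or design effect appears among the inputs.

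Implementation {16c} says: "Clusters or communities will be randomized and not individual participants". Sequence generation {16a} takes five communities from each LGA, forms them into two geographically separate groups, and allocates one group to each arm. The primary analysis of blood pressure control in Statistical methods {20a} is a random-effect logit model comparing the two arms.

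**The concern.** Every input to the calculation is printed, so the result can be checked, and 50 looks too small for 30% versus 60% at 90% power even before attrition. A figure that small also leaves no room for the clustering that the design creates. In addition, the scaling from 50 per arm to 100 per LGA presents each LGA as a powered comparison of its own.

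The 90% power is the published justification for the trial's size. If it is wrong, readers are given a property the design does not have. Conclusions for a single LGA or state would then rest on a calculation that does not support them.

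**Working it through.** **Inputs from the protocol.** Sample size {14}: p1 = 0.30, p2 = 0.60, Z = 1.96 and 1.28, attrition 10%, 50 per arm, 100 per LGA, 600 in all. Sequence generation {16a}: five communities per LGA in two groups, one per arm. This means about 100/5 = 20 patients per community and 50 per randomised group, or 18 and 45 after 10% attrition. Over six LGAs there are 12 randomised groups.

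**Trying to reproduce the 50.**

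- Unpooled variance: (1.96 + 1.28)² × (0.21 + 0.24) / 0.30² = 10.4976 × 0.45 / 0.09 = 52.5, so 53 evaluable. With attrition, 53/0.9 = 58.9, so 59.
- Pooled variance under the null only: 55.6; 55.6/0.9 = 61.8, so 62 (63 if 55.6 is first rounded up to 56).
- Pooled variance throughout: 10.4976 × 2 × 0.45 × 0.55 / 0.09 = 57.7; 57.7/0.9 = 64.2, so 65.
- With continuity correction: 63, then 70.

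None gives 50, and 50 is below the smallest of them before attrition. Values near 50 appear only if a stated input is changed. For example, 85% power gives 44.9/0.9 = 49.9, one-sided 5% gives 48 to 52 depending on the variance form, and 80% power with pooled variance throughout gives 49. Which of these, if any, produced the 50 cannot be determined.

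**Power with 50 recruited, ignoring clustering.** With 45 evaluable, the standard error is √(0.45/45) = 0.10 and 0.30/0.10 − 1.96 = 1.04, so power is 85%. It is 83% with pooled variance under the null, and 82% by exact enumeration of the uncorrected chi-squared test. With no attrition at all, 50 per arm gives 88.5% (unpooled) or 86.6% (pooled).

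**Clustering within one LGA.** The protocol gives no intracluster correlation (ICC), so the values here are assumptions. The design effect is 1 + (m − 1) × ICC, the effective sample is 45 divided by it, and the power uses the unpooled normal approximation.

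| ICC (assumed) | Design effect, m = 18 | LGA power | Design effect, m = 45 | LGA power |
|---|---|---|---|---|
| 0.01 | 1.17 | 79% | 1.44 | 70–71% |
| 0.02 | 1.34 | 74% | 1.88 | 59% |
| 0.05 | 1.85 | 60% | 3.20 | 39% |

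The m = 45 column is optimistic. It treats the ICC as known, whereas one group per arm leaves no degrees of freedom to estimate between-group variation.

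**The whole trial.** There are 270 evaluable per arm. Taking the 12 randomised groups as clusters (m = 45), the variance of the difference is (0.45/45) × design effect / 6. Power comes from the noncentral t distribution, with 5 df for six LGA pairs or 10 df for an unpaired comparison of 12 groups. The last column takes the communities as clusters (m = 18, 28 df).

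| ICC (assumed) | 12 groups, 5 df | 12 groups, 10 df | 30 communities, 28 df |
|---|---|---|---|
| 0.02 | 99% | >99% | >99% |
| 0.05 | 90% | 96% | >99% |
| 0.10 | 72% | 81% | 99% |

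**The case against.** The strongest reply is that the trial recruits 300 per arm, about five times the 59 needed without clustering. With 270 evaluable per arm, a design effect of up to 270/52.5 = 5.1 still leaves 90% power by the normal approximation. That corresponds to an ICC of about 0.24 with communities of 18, or 0.09 with groups of 45. The protocol announces no LGA-level or state-level test, and the LGA reading comes only from the scaling sentence. Clustering is handled in the analysis by the random-effect and mixed models. The 5-df figures are the most pessimistic of the defensible choices: the protocol does not describe a paired analysis, and the calculation takes no credit for any gain from pairing.

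Much of this stands. The trial as a whole should not be called underpowered, and the 72% belongs beside the more favourable columns. But the objection does not rescue the 50. A model that allows for clustering at analysis does not correct a sample size that omitted it. The scaling sentence does put 50 versus 50 inside each LGA, and no other level is given for the stated power. That the total may suffice is something the protocol neither claims nor shows.

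**Conclusion.** The paragraph is wrong as written. On the protocol's own inputs the requirement is at least 53 evaluable and 59 recruited per arm, against a stated 50, which gives about 83 to 85% power after attrition rather than 90%. This part needs no assumption.

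Clustering is not in the figure, since 50 is below the individually randomised number. Under an assumed ICC of 0.01 to 0.05, LGA-level power falls to between 79% and 60% (communities as clusters) or roughly 70% and 39% (randomised groups as clusters). The overall comparison is likely adequate over most of the assumed range. It falls below 90% only if the randomised groups are the clusters and the ICC exceeds about 0.05 (paired, 5 df) or approaches 0.10 (unpaired or normal approximation).

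**What to change.** Keep the 600 patients and rewrite the sample size paragraph to say four things:

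1. Without clustering, 30% versus 60% at two-sided 5% and 90% power needs 53 evaluable, or 59 recruited, per arm; 50 recruited gives about 85%.
2. The powered comparison is the overall one, 300 versus 300, in 12 randomised groups forming six LGA pairs.
3. Its power is shown over an assumed and justified ICC range, with the cluster definition, cluster size, design effect and degrees of freedom given.
4. LGA and state results are descriptive.

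The cost is rewording only. No patients are added and no study procedure changes, though the stated power becomes less favourable.

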### Recruitment {15}

Persons found to be hypertensive during baseline survey will be noted and contact address taken including the phone contact. Subsequently, they will be invited to the primary health facility in their neighbourhood for recruitment into the study (Intervention arm). In addition, the trained CORPs will screen and refer community members found to have high blood pressure to the primary healthcare facilities in the community (intervention arm) or health facility of their choice (control arm). The CORPs will carry out sensitization campaign in the community through visits to community stakeholders including the community chiefs, heads of religious bodies, leaders of artisans, head of community structures such as Chairman of Landlord Associations, and talks in churches, mosques and community meetings to intimate them of the programme and conduct blood pressure screening. The CORPs shall be provided with identification poster for display in front of their houses to indicate that blood pressure screening service is available. If the required number of hypertensive patients to be recruited in a community is not achieved, the neighbouring community may be co-opted and the CORP mobilized to cover the community as well. At the health facility, patients presenting with other ailments or walk-in patients or self-referred patients who present at the health facilities found to be hypertensive shall be requested to participate in the study. The physician/healthcare worker will confirm diagnosis and commence antihypertensive medications.

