#### Community members

The community members will participate at the three phases of the study.

For the base- and endline surveys, participants will be consenting residents of the community aged ≥18 years. A resident will be someone who has been living in the community for 6 months or more. Those who are sick at time of survey, mentally challenged or have communication challenge and pregnant women will be excluded from the survey. In addition, at endline survey, a subgroup of participants in the intervention arm will be randomly selected to participate in focus group discussions and in-depth interviews to explore their acceptability and perception of quality of the CORPs delivered follow-up care, as well as perceived challenges to implementation and sustainability.

For recruitment into the intervention, those found at community screening to have elevated blood pressure and same confirmed in the health facility, old patients receiving treatment and not controlled or not on treatment will be eligible for recruitment. They must plan to reside in the community for at least 1 year after enrollment and willing to participate in the home-based follow-up care by CORPs. To be excluded are patients with clinically established complications and other cardiovascular diseases, patients needing or on special medical services and pregnant women. The health workers to recruit at the health facilities will be medical officers of health and nurses involved in the care of adults in the health facilities. They will be trained on diagnosis, treatment and prevention of hypertension as well as use of the national guideline for treatment of hypertension.

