## Interventions

### Explanation for the choice of comparators {6b}

Comparators will be adults aged 18 years and above who are living in the control communities and receiving usual care for the management of hypertension.

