## Assignment of interventions: allocation

### Sequence generation {16a}

The unit of randomization will be the community. A total of 10 communities (five from each LGA) will be randomly selected from the list of communities from a ward obtained from the Local Government secretariat. The selected communities from each LGA will be grouped into two non-contiguous groups based on geographical distance between communities. One group will be randomly assigned to intervention and another to control. This will ensure that intervention communities are closed together but at far distance from control communities to minimize contamination. The final randomization of intervention and control communities will be done by a statistician who is not involved in the implementation of field activities. Assignment of communities to either the intervention or control arm will be done after the baseline survey. Given the nature of the intervention, it is not possible to blind the CORPs who will be involved in the delivery of the intervention.

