### Concealment mechanism {16b}

Clusters (communities) will be randomly allocated to intervention and control group by the study statistician using a digital sealed envelope. This will be done after the collection of baseline data and just before the commencement of the intervention phase.

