The population characteristics of the urban and rural areas could differ especially with age and sex bearing in mind population migration factors and dynamics. This may distort the true effect of the intervention on outcome as CVD risk factors varies in these groups of people. This will be adjusted at analysis using multilevel analysis with random effect model. Bias in the intervention study will be minimized by randomization. The possible contamination between control and intervention arm will be reduced by grouping/clustering the communities before randomization and ensuring buffer zones exist between them to limit diffusion.

Cluster-randomized design is appropriate for this study which by nature is evaluating the effectiveness of an interventions in a “real-world setting” [48], and meant to provide health education at both community and individual levels. In addition is the fact that it is also an effective way to avoid contamination. The limitations associated with its use such as prevention of interference shall be giving much attention at analysis.

In conclusion, this study stands to provide evidence-based information for scaling up task sharing as well as community-clinical linkage in the control of hypertension in Nigeria. It is expected that this intervention will bring about early detection of hypertension, reduction in mean blood pressure and an increase in the proportion of patients with controlled blood pressure. In addition, we expect an improvement in the mean quality of life score; healthy lifestyle and competent CORPs as well as the reduced mean cost of treatment of hypertension in the intervention arm of the study. All of these will inform policy review to guide the control of hypertension and reduction in cardiovascular diseases risk in Nigeria.

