## Trial status

The study protocol version number is 3 (December 01 December 2019). The study commenced in August 2020 and expected to be completed in July 2022. The recruitment start date for the cluster RCT is September 2021 and end date is February 2022. Formative phase has been concluded. The recruitment for the intervention has not started.

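### Patients are recruited after communities are allocated, by staff who know the arm and through arm-specific routes, and control eligibility is unclear, so the compared patients may not be alike

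*Protocol article*

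**What the plan says.** **Order of events.** Sequence generation {16a}: "Assignment of communities to either the intervention or control arm will be done after the baseline survey". Concealment mechanism {16b}, on the allocation of clusters: "This will be done after the collection of baseline data and just before the commencement of the intervention phase". Table 2, under Participant timeline {13}, puts the baseline studies in quarter 2, recruitment of patients in quarter 3 and follow-up visits from quarter 4.

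**Who enrols.** Implementation {16c}: "Allocation will be done by the statistician while participants will be enrolled by CORPS and health workers at the primary health centres". Sections {16a} and {17a} both state that the CORPs cannot be blinded.

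**Routes.** Recruitment {15} says that persons found hypertensive in the survey are noted with contact details, and that afterwards "they will be invited to the primary health facility in their neighbourhood for recruitment into the study (Intervention arm"). No such invitation is given for control communities. The same section and Table 1 send CORP-screened people with high pressure to the designated primary health centre in the intervention arm and to a facility of their own choosing in the control arm.

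**Eligibility.** Under Eligibility criteria {10}, Community members, the criteria for recruitment into the intervention are: elevated pressure confirmed at a facility, treated but uncontrolled, or untreated; no established complications or other cardiovascular disease; and being "willing to participate in the home-based follow-up care by CORPs". Section {6b} describes the other arm in these terms: "Comparators will be adults aged 18 years and above who are living in the control communities and receiving usual care" for hypertension.

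**Safeguard claimed.** Discussion: "Bias in the intervention study will be minimized by randomization".

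**The concern.** Randomising communities makes the communities comparable in expectation. It does the same for patients only if patients are identified before allocation is known, or are selected afterwards in the same way in both arms by people who do not know the arm. Here the people who approach patients know the arm, the way in depends on the arm, and one criterion (accepting home visits) is meaningful only where home visits are offered.

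Both primary outcomes are exposed: the proportion with controlled pressure and the mean change in pressure at 6 months. Each depends on entry pressure, on treatment status at entry and on motivation. The direction cannot be fixed in advance:

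- If intervention patients are all uncontrolled at entry and some controls are already controlled, the effect on final control is understated. Regression to the mean would meanwhile flatter the intervention on change from baseline.
- If intervention patients are selected as willing and free of complications, the effect is overstated.

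**Working it through.** **Step 1: is allocation known when patients are approached?** No sentence says so outright; it follows from three places.

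- Allocation comes after the baseline survey ({16a}, {16b}), and recruitment comes in the quarter after the survey (Table 2).
- The routes in {15} are labelled by arm, which is workable only if the arm is known at first contact.
- Table 1 gives the follow-up-care training of CORPs and the guideline training of facility staff to the intervention arm only. Table 2 places selection and training of CORPs and training of health workers before recruitment.

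The sealed envelope in {16b} conceals the allocation of communities from whoever allocates them. It does not conceal the arm from whoever later enrols patients.

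**Step 2: routes side by side.**

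| Route | Intervention | Control |
|---|---|---|
| Hypertensive in baseline survey | Invited to the neighbourhood primary health facility for recruitment | No invitation stated |
| CORP screening | Referred to designated primary health centre | Referred to facility of choice |
| Place of enrolment in {16c} | Primary health centre | Primary health centre, though referral may be elsewhere |

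**Step 3: scale (hypothetical).** The plan's own figures in Sample size {14} are 30% controlled without the package and 60% with it, a planned difference of 60 - 30 = 30 points. The 50 per arm per LGA x 2 LGAs x 3 states gives 300 per arm and 600 in all. After 10% attrition, 300 x 0.90 = 270 per arm are evaluable.

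Assumptions, none from the documents: every intervention patient is uncontrolled at entry; a share c of controls is already controlled; a share q of those stay controlled; a share r of uncontrolled patients become controlled in either arm; there is no treatment effect. Then

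- intervention rate at 6 months = r
- control rate = c x q + (1 - c) x r
- difference (control minus intervention) = c x (q - r)

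With (q, r) = (0.70, 0.20) or (0.80, 0.30), q - r = 0.50, so:

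| c | Difference | Rates, first pair | Rates, second pair | Chance of a significant result |
|---|---|---|---|---|
| 0.10 | 5 points | 20% v 25% | 30% v 35% | 24-29% |
| 0.20 | 10 points | 20% v 30% | 30% v 40% | 68-77% |
| 0.30 | 15 points | 20% v 35% | 30% v 45% | 95-98% |

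The last column is for a two-sided 5% test of two proportions with n = 270 per arm: Φ((d - 1.96 s0)/s1) + Φ((-d - 1.96 s0)/s1), where d is the difference, s0 = √(2p̄(1 - p̄)/n) and s1 = √((p1(1 - p1) + p2(1 - p2))/n). For 30% v 40%: s0 = 0.0410, s1 = 0.0408, and (0.10 - 1.96 x 0.0410)/0.0408 is about 0.48, which gives 68%. Clustering is ignored, so this column shows scale only. The illustration covers one mechanism, which works against the intervention. The documents give no basis for a figure on willingness, which would work the other way.

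**Step 4: how many patients could be enrolled before allocation is disclosed?** Inputs: 1704 adults surveyed (Abstract, Methods), prevalence 28.9% (Background {6a}), and 30% controlled ({14}), hence 70% not controlled.

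- 1704 x 0.289 = 492 hypertensive; x 0.70 = about 345 uncontrolled.
- With the Ibadan range in {6a}: 1704 x 0.204 x 0.70 = about 243; 1704 x 0.331 x 0.70 = about 395.

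This is before exclusions and refusals, so the list falls short of 600 by at least 205 to 357 patients (255 at the central figure).

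**The case against.** **The eligibility criteria may already cover both arms.** The Community members section sets criteria by phase, and {14} uses intervention phase for all 600 patients. Section {6b} answers why a comparator was chosen and is not an eligibility list. A reader might infer that controls enter under looser rules and may already be controlled. The documents do not say that; they leave it unclear. What stands is that the willingness criterion fits only one arm and that {6b} has not been reconciled with {10}.

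**Confirmation is not shown to be missing for controls.** A reader might infer that intervention patients are confirmed at a second visit and controls are not. The Blood pressure section refers every survey participant with elevated pressure for confirmation, the Abstract includes diagnosis in control-arm usual care, and the closing sentence of {15} on confirming the diagnosis names no arm. It is also tempting to put 10 to 13 points on regression to the mean. Under assumed systolic means of 128-130, between-person SDs of 16-18 and visit-to-visit SDs of 8-12, 27-42% of people chosen on one reading fall below 140 later, against 16-29% after a confirmatory reading. That requires single-reading entry for controls, which no section states, and no treatment, although usual care includes treatment. It is not used here.

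**There are mitigations.** CORPs are trained and screen in both arms, so one detection route is partly shared. The plan compares baseline characteristics to choose adjustment variables ({20a}), uses difference-in-difference and mixed models for blood pressure ({20b}) and promises multilevel adjustment (Discussion). These help with measured differences but cannot restore balance on willingness or care-seeking.

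**This is a condensed article.** The flow chart is not shown, and a control enrolment procedure may be set out in the full protocol. The point therefore rests on the explicit timing and arm labels more than on silence.

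**Conclusion.** The concern holds for timing and route: patients are recruited after allocation, by staff who know the arm, along routes that differ by arm. For eligibility it holds only as an ambiguity between {10}, {6b} and {14}. The compared patients may differ in entry pressure, treatment status and willingness, and the Discussion's reliance on randomisation does not meet that risk. It would go too far to say that the arms are known not to be comparable.

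The direction is unknown. The 5 to 15 points in 6-month control, against a planned 30, rests wholly on the assumed case mixes above. It shows that the risk is large enough to matter, not what this trial would experience. Trial status records "The recruitment for the intervention has not started", so on the article's own account the entry rules could still be settled before the first patient.

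**What to change.** 1. State that the inclusion and exclusion criteria in {10} apply to both arms. Ask about home follow-up as a conditional question (whether the patient would accept it if it were offered) before allocation is disclosed. Reconcile {6b} with this.
2. Before allocation is disclosed, invite and consent the eligible hypertensives from the baseline survey in all communities through a neutral enrolment contact. This replaces the invitation labelled for the intervention arm. Deleting the label alone would not do, because it would draw controls to the neighbourhood primary health centre, against usual care at a facility of choice. If allocation has already been disclosed (the article does not say), the survey list still predates it and should be approached identically in both arms.
3. Recruit the remainder in both arms under the same criteria and the same recorded entry-pressure rule, and flag them as post-allocation recruits.
4. Adjust the primary between-arm model for baseline systolic pressure, and repeat it in the pre-allocation list as a sensitivity analysis.

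Cost: protocol and consent wording, and recording of entry pressure for control patients. The target of 600 is unchanged. The sensitivity set is smaller and less precise (about 345 at most on the central figures), and the post-allocation recruits remain open to selection, which is why they must be identifiable.

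### The top-up rule lets a community that was never allocated join an arm after allocation, and does not keep it out of the ground between the arms

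*Protocol article*

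**What the plan says.** Under Sequence generation {16a}, "The unit of randomization will be the community". On sampling, "A total of 10 communities (five from each LGA) will be randomly selected from the list of communities". Then "The selected communities from each LGA will be grouped into two non-contiguous groups based on geographical distance between communities", and one group is randomised to each arm. The stated purpose is that "intervention communities are closed together but at far distance from control communities to minimize contamination". The Discussion relies on the same protection and speaks of "ensuring buffer zones exist between them to limit diffusion".

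On timing, Concealment mechanism {16b} says of the allocation: "This will be done after the collection of baseline data and just before the commencement of the intervention phase".

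Recruitment {15} then gives the shortfall rule: "If the required number of hypertensive patients to be recruited in a community is not achieved, the neighbouring community may be co-opted". Staffing of the added community is settled in the same sentence, with "the CORP mobilized to cover the community as well". The section does not say which neighbour qualifies, who decides, or whether any location is excluded. The rule is not restricted to one arm.

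**The concern.** The comparison between arms rests on two protections: the clusters in each arm were put there by chance, and the arms are physically apart. The shortfall rule weakens both.

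A community added during recruitment was not in either group when the allocation was drawn. It joins an arm because of where it lies and because its neighbour recruited poorly. Whether a community falls short, and which neighbour is then used, can depend on how recruitment runs in that arm. Patients from it are therefore not protected by the randomisation.

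The separation of the arms also depends on unselected communities lying between the two groups. A neighbour of a trial community may be one of these. If an intervention CORP is extended into it, screening, community education and group sessions move closer to the control communities.

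**Working it through.** **Order of steps.** The article does not say in one sentence that co-opting happens after allocation, but three places together leave no other reading.
- Allocation comes after the baseline survey and just before the intervention phase (Sequence generation, Concealment mechanism).
- Table 2 puts baseline work in the second quarter, recruitment in the third, and follow-up visits in the fourth and fifth.
- Recruitment {15} describes referral by arm: to the local primary facility in the intervention arm, to a facility of the person's choice in the control arm. The arm must therefore be known while patients are being recruited, and the trigger for co-opting is a shortfall in that recruitment.

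**Status of a co-opted community.** Against the steps in Sequence generation, it was not placed in a group, not part of the allocation and not covered by the baseline community survey. It takes the arm of the community whose CORP covers it. Not having been in the random draw of five also matters, but for representativeness; the bias argument rests on its absence from the allocation.

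**Location.** A neighbour can lie on the side away from the other group, within its own group's area, or on the side facing the other group. Only the last is in the buffer. The rule permits all three.

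**Which arm.** In Table 1, control CORPs screen and refer only; monthly follow-up, counselling and messages are confined to the intervention arm. Contamination is therefore mainly a matter of the intervention arm extending towards the control group.

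**Size.** Inputs from Sample size {14} and Sequence generation: 50 patients per arm per LGA (50 × 2 arms × 2 LGAs × 3 states = 600) and five communities per LGA. Assumptions: the five are split as evenly as possible, 2 against 3, and patients are spread equally over communities.

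The stated inputs do not reproduce the plan's 50. The unpooled formula gives (0.30 × 0.70 + 0.60 × 0.40) × (1.96 + 1.28)² / 0.30² = 0.45 × 10.4976 / 0.09 = 52.5, so 53, and 53 / 0.9 = 58.9, so 59 after attrition. The pooled form gives 56, and 63 after attrition. That is a separate matter; 50 is used here as the quota that triggers the rule.

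With k communities in the LGA-arm and a proportional shortfall s in one of them:
- top-up patients = s × 50 / k
- share of the LGA-arm = s / k, which does not depend on the 50

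| Shortfall s in one community (assumed) | k = 3 (50/3 = 16.7 each) | k = 2 (50/2 = 25 each) |
|---|---|---|
| 10% | 1.7 (3.3%) | 2.5 (5%) |
| 20% | 3.3 (6.7%) | 5 (10%) |
| 50% | 8.3 (16.7%) | 12.5 (25%) |
| 100% | 16.7 (33.3%) | 25 (50%) |

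**The case against.** The strongest reply is that this is a contingency, since the text says only that a neighbour may be used, and that whole groups are allocated. A group's members lie close together, so a neighbour will often fall inside or beside its own group's area and simply enlarge an existing cluster. A condensed article may also leave limits on such extensions to the full protocol.

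Part of this stands. A reader might infer that the rule flatly contradicts the buffer zones, or that any neighbour must lie in one. The documents do not support that: a buffer lies only on the side facing the other arm, and the fault is that the rule excludes nothing.

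Four other inferences also go too far.
- **Unblinded staff choose the community.** CORPs cannot be blinded, and they and health workers enrol patients, but no decision-maker is named for co-opting.
- **Co-opted patients have no baseline data.** What is missing is the community survey. Blood pressure is confirmed at the facility, and blood, urine and ECG are planned at recruitment or baseline, although Table 1 leaves unclear how far these reach controls. Walk-in and self-referred patients from the original communities need not have been surveyed either.
- **A co-opted community supplies a third to a half of an LGA-arm.** That requires the original community to recruit nobody.
- **The planned 30-point difference (60% − 30%) shrinks by a known amount.** A drop to 24 points, 30 × (1 − 0.20), needs an assumed 20% of controls to be exposed and to gain the full effect. Much of the package, such as home visits and messages, requires enrolment.

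The enlargement argument does not remove the problem. The article equates clusters with communities, and an enlargement made after allocation is still not randomised. Nor is this an omission: the article states a rule which, followed as written, permits the result described.

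**Conclusion.** The point holds in a limited form and should be corrected. As written, the rule can bring communities into an arm after allocation that were not part of it, and does not stop the intervention arm from extending towards the control group.

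The effect scales with the shortfall. At an assumed 20% shortfall in one community it concerns about 3 to 5 patients, 7 to 10% of one LGA-arm; the ceiling of 33 to 50% applies only to a community that recruits nobody. These figures rest on the 2-against-3 split and equal quotas. The documents give no basis for putting a number on the resulting bias or dilution. That co-opting follows allocation is inferred from the order of steps, and firmly so. That a co-opted community would lie in the buffer is a possibility only.

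**What to change.** Replace the shortfall rule in Recruitment {15}:

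- Before the allocation envelope is opened, the statistician lists, for each of the two groups in each LGA, an ordered set of reserve communities on the side away from the other group. Any community in the buffer or adjacent to the other group is excluded.
- Reserves are allocated with their group and used in list order, under the same rule in both arms.
- If no reserve is eligible, the shortfall is made up from other communities in the same allocated group.
- Top-up patients are analysed in their allocated group, flagged in the data, and left out in a sensitivity analysis.

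Trial status says that recruitment for the intervention had not started, so the rule can be changed before it is used. If allocation has already been made, the statistician, who has no field role, can still draw up the list before recruitment opens. Reserves listed then would not have been randomised, which makes the flag and the sensitivity analysis more important.

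The cost is drawing up the list. The small downside is slower recruitment where eligible reserves are few, which may happen because communities are drawn from ward lists. The article gives no figure for the required distance, so the statistician will need to define the buffer when making the list.
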